### **5.3 Selection of Trial Population**

#### **5.3.1 Recruitment Procedures**

Recruitment procedures and materials will be submitted for Ethics Committee (EC) approval before implementation.

#### **5.3.2 Participant Information and Consent**

Informed consent is the process by which a subject/parent/legal representative voluntarily confirms his or her willingness to participate in a particular trial, after being informed of all relevant aspects of the trial. Informed consent is documented by means of a written, signed and dated ICF.

Written informed consent must be provided for each subject before being included in the trial. For all subjects, an ICF will be signed by one parent/legal representative and by an independent witness if the parent/legal representative is illiterate. In addition, one separate assent form will be signed by subjects aged between 7 and 12 years and another will be signed by subjects aged between 13 and 17 years.

Prior to signing the assent/consent form, the subject/parent/legal representative must be informed by the appropriate study personnel about the nature and purpose of the trial in accordance with GCP and must have sufficient time and opportunity to ask any questions.

In addition, if new information becomes available that may be relevant to the subject's willingness to continue participation in the trial, this will be communicated in a timely manner to the subject. The communication of this information will be provided and documented via a revised consent form or addendum to the original consent form.

A sample ICF (for all subjects) and a sample assent forms (for subjects aged 7 to 12 years and subjects aged 13 to 17 years) are provided in Appendix 2.

ICFs and assent forms will be provided in duplicate (the original will be kept by the Investigator and the copy kept by the subject and/or the subject's legally acceptable representative).

### 5.3.3 Inclusion Criteria

#### *All subjects:*

- 1) Able to attend all scheduled visits and to comply with all trial procedures.

#### *Children/Adolescents aged $\geq 2$ years to $< 18$ years:*

- 2) Aged  $\geq 2$  years to  $< 18$  years on the day of inclusion.
- 3) Informed Consent Form signed by one parent or another legal representative and by an independent witness if the parent/legal representative is illiterate. In addition, two assent forms signed: one signed by subjects aged between 7 and 12 years and the other signed by subjects aged between 13 and 17 years.
- 4) For a female, inability to bear a child or negative urine pregnancy test (as applicable)a.
- 5) For a female of child-bearing potential, use of an effective method of contraception or abstinence for at least 4 weeks prior to the first vaccination and at least 4 weeks after the last vaccination (as applicable)b.

#### *Infants/toddlers aged $\geq 6$ months to $< 2$ years:*

- 6) Aged  $\geq 6$  months to  $< 2$  years on the day of inclusion.
- 7) Born at full term of pregnancy ( $\geq 37$  weeks) with a birth weight  $\geq 2$  kg.
- 8) Informed consent form signed by one parent/legally acceptable representative and an independent witness if the parent/legally acceptable representative is illiterate.
- 9) Subject who completed vaccination according to the national immunization schedule.

---

a To be considered as unable to bear a child, a subject must be pre-menopausal or have undergone surgical sterilization (tubal ligation or hysterectomy).

b Effective methods of contraception include oral contraception (pill), Intra-Uterine Device, diaphragm or condoms used in conjunction with sponge, contraceptive foam or cream, hormonal implants, or transdermal patch.

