| Diary Card (DC)/
Memory Aid (MA):
Provided:
Checked:
Collected: | DC1                                      | DC1      | DC2
DC1       | DC2      | MA1
DC2   | MA1       | MA2
MA1 | DC3
MA2           | MA3
DC3   | MA3**              |
| Injection site reactions and Systemic Event Assessment                      | √                                        | √        | √                | √        | √            |           |            |                      | √            |                    |
| Reportable Concomitant Medication                                           | √                                        | √        | √                | √        | √            |           |            | √                    | √            |                    |
| Termination Record                                                          |                                          |          |                  |          | √            |           | √          |                      | √            |                    |
| Serious Adverse Events                                                      | Collected through the whole study period |          |                  |          |              |           |            |                      |              |                    |

- 
- \* A telephone call or a visit at the site is to be arranged 6 months after the booster vaccination to collect information on SAEs. In the event of an SAE, the Investigator may arrange a visit with the subject to obtain further information.
  - † In addition, one assent form to be signed by subjects aged 7 to 12 years and another assent form to be signed by subjects aged 13 to 17 years.
  - ‡ For adolescents of child-bearing potential only.
  - § Limited to medical interview if visit replaced by 'phone call.
  - \*\* MA3 to be returned by mail if visit replaced by 'phone call.

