### 5.1.3 Visit Procedures

#### *V01: First vaccination (D0) and blood sampling:*

- The Investigator or delegate will:
  - 1) Obtain informed consent and/or assent (as described in Section 5.1.2) by presenting the trial to the subject and/or subject's parent/legal representative and/or independent witness, as applicable, answer any questions, and ensure that the subject and/or subject's parent/legal representative has been informed of all aspects of the trial that are relevant to the decision to participate.
  - 2) Date and sign the ICF, after it has been dated and signed by the subject and/or subject's parent/legal representative and/or independent witness, as applicable (the Investigator will retain the original of this document and will give the copy to the subject or subject's parent/legal representative).
  - 3) Take the subject's axillary temperature and record in the source document and CRF.
  - 4) Perform a urine pregnancy test for subjects of child-bearing potential (as applicable).
  - 5) Check all inclusion and exclusion criteria through physical examination and medical interview.
  - 6) Allocate a trial inclusion number to the subject (see Section 6.6).
  - 7) Record the subject's initials, subject number, date of birth, height, weight, sex, ethnic origin (Caucasian, Asian, Black, or other), past and current significant medical history, and all information related to points 3 to 5 (above) in the source document and then in the CRF.

---

a The timing and type of booster to be determined following results from GPA01 and GPA02

- 8) Record details of any influenza-like illness (ILI) and inter-pandemic influenza vaccination (including dates of occurrence) in the CRF.
- 9) Take a blood sample in a dry silicone tube from all subjects for serology evaluation (7 mL for Groups 1 and 2; 2 mL for Group 3). Take a further 2 mL sample in a sodium heparin tube from subjects in Group 3 only for CMI response analysis.
- 10) If blood sampling for serology cannot be performed, the subject will not be vaccinated. In this case, his/her subject number will not be reassigned.
- 11) Scratch the randomization list to define the vaccine dose corresponding to the subject's number.
- 12) Administer the vaccine dose corresponding to the subject's treatment group, and preferably on the side opposite to that of blood sampling (for subjects receiving the vaccination in the deltoid muscle only – see Section 6.2.2).

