***V08: Booster vaccination and blood sampling (D365, M12):***

- The Investigator or delegate will:
  - 1) Interview the subject and/or subject's parent/legal representative, requesting information concerning any SAE that may have occurred since V07.
  - 2) Collect and review MA2, used by the subject and/or subject's parent/legal representative since V07 and record any additional information and/or discrepancies in source documents.
  - 3) Perform a urine pregnancy test for subjects of child-bearing potential only.
  - 4) Check all temporary and definite contraindications through physical examination and medical interview (in the event of temporary contraindications, the vaccination will be delayed; in the event of definite contraindications, the vaccination will not be performed).
  - 5) Perform a physical examination and complete the source document.
  - 6) Record details of any influenza-like illness (ILI) and inter-pandemic influenza vaccination (including dates of occurrence) in the CRF.
  - 7) Take a blood sample in a dry silicone tube from all subjects for serology evaluation (7 mL for Groups 1 and 2; 2 mL for Group 3).
  - 8) Take the subject's axillary temperature and record it in the source document and CRF.
  - 9) Scratch the randomization list to define the booster dose corresponding to the subject's number (if applicable)a.
  - 10) Administer the vaccine dose corresponding to the randomization (if applicable) and preferably on the side opposite to that of blood sampling (for subjects receiving the vaccination in the deltoid muscle only – see Section 6.2.2).
  - 11) Affix the corresponding detachable label in the source document and CRF.
  - 12) Ensure the 30-minute observation period following vaccination is observed.
  - 13) Complete the source document and CRF.
  - 14) Record any injection site reactions, systemic reactions/events, and prohibited concomitant medications and any analgesics/antipyretics/NSAIDs taken (see Section 6.8) in the CRF.
  - 15) Provide the subject and/or subject's parent/legal representative with the DC3 to be filled in until V09, a digital thermometer and a ruler, and instruct the subject how to use these tools and how to complete the DC.

---

a If more than one type of booster is used, this is to be defined following results from GPA01 and GPA02.

16) Remind the subject and/or subject's parent/legal representative to contact the Investigator in the event of any SAE between V08 and V09.

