#### **5.3.6.5 Follow-up and Reporting of Pregnancies**

Pregnancy is an exclusion criterion for enrolment in this trial, but subjects of child-bearing age could potentially become pregnant during their period of participation. Although pregnancy is a normal state, pregnancy occurring during the trial is to be recorded as an AE (but not as a SAE). Any complications during pregnancy (e.g. gestational diabetes or eclampsia) are also to be considered as AEs, however, these complications could result in the event being a SAE.

The Investigator is required to complete Part 1 of the "Initial Pregnancy Report Form" as soon as he/she is aware that the subject is pregnant. Part 1 contains information that includes the date of the last menstrual period, expected date of delivery, and the dates of vaccination. Part 2 contains follow-up information about delivery and newborn or pregnancy termination and is required to be completed at a follow-up after the due date.

---

a Voluntary withdrawal is also referred to as "withdrawal of consent" or "drop-out"

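### Footnote a to inclusion criterion 4 defines inability to bear a child with the wrong word (*pre-menopausal*), so read literally practically every girl under 18 meets the criterion whatever her pregnancy test shows

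*Protocol*

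**What the plan says.** Criterion 4 in Section 5.3.3 applies to subjects aged 2 to under 18 years: "For a female, inability to bear a child or negative urine pregnancy test (as applicable". Its footnote a gives the only explanation of the first alternative: "To be considered as unable to bear a child, a subject must be pre-menopausal or have undergone surgical sterilization". The synopsis carries the same criterion without a footnote.

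Other parts of the protocol deal with pregnancy separately:

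- **Visit procedures (Section 5.1.3).** V01 step 4 reads "Perform a urine pregnancy test for subjects of child-bearing potential (as applicable". Step 5 follows with "Check all inclusion and exclusion criteria through physical examination and medical interview". The urine test is repeated at V03 (step 6) and at the booster visit (V07 step 4 in the 6-month design, V08 step 3 in the 12-month design). The V08 step reads "Perform a urine pregnancy test for subjects of child-bearing potential only".
- **Flow-charts (Figures 1 and 2).** The urine-test row is ticked at V01, V03 and the booster visit, with the footnote "For adolescents of child-bearing potential only".
- **Criterion 5 and its footnote b (Section 5.3.3).** Females of child-bearing potential must use contraception or be abstinent. The footnote begins "Effective methods of contraception include oral contraception (pill), Intra-Uterine Device, diaphragm or condoms".
- **Definite contraindications (Section 5.3.6.1).** A positive urine test bars the second and booster vaccinations.
- **Section 5.3.6.5.** "Pregnancy is an exclusion criterion for enrolment in this trial, but subjects of child-bearing age could potentially become pregnant".
- **Exclusion criteria (Section 5.3.4).** The list of 17 items includes breast-feeding mothers but not pregnancy.

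**The concern.** A footnote that says who counts as unable to bear a child should separate girls who have not reached menarche, or who are sterilized, from those who could be pregnant. *Pre-menopausal* cannot do that in subjects under 18, because menopause lies ahead of practically all of them. The word that fits a paediatric trial is *pre-menarchal*.

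Criterion 4 is operative text, checked before the first dose of an investigational vaccine. It is also the only listed eligibility criterion that turns on pregnancy. If its first limb takes in practically every girl, the second limb (a negative test) decides nothing. A site or monitor applying the text as printed could record a girl with a positive test as meeting criterion 4, although Section 5.3.6.5 says that pregnancy excludes her.

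**Working it through.** No arithmetic applies, and the plan has no figure to reproduce. The check sets the texts side by side.

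**Step 1: what criterion 4 requires.** It is met if A or B holds, where A is inability to bear a child and B is a negative urine test.

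**Step 2: what footnote a makes of A.** As a definition, A holds if the subject is pre-menopausal or surgically sterilized. The wording (*must be*) could also be taken as a necessary condition only. In that case the footnote separates nobody, since practically every girl satisfies it, and sites are left with no usable definition. It fails its purpose on either reading. The table uses the first reading, which is how a site would normally use such a footnote.

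**Step 3: apply it to the girls who may present.**

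| Girl under 18 | Urine test | Criterion 4 as printed | Criterion 4 with *pre-menarchal* |
|---|---|---|---|
| Before menarche | not needed | met by A | met by A |
| Sterilized | not needed | met by A | met by A |
| After menarche, not sterilized | negative | met by A and B | met by B |
| After menarche, not sterilized | positive | **met by A** | **not met** |

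Only the last row changes the eligibility result. It is the row for which the criterion exists.

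**Step 4: look for another listed rule that catches the last row at enrolment.** Section 5.3.4 does not list pregnancy. Criterion 5 concerns contraception or abstinence, not pregnancy status. The contraindications in Section 5.3.6.1 are verified before the second and booster vaccinations, not before the first. What remains is the statement in Section 5.3.6.5 that pregnancy excludes, and no item in the exclusion list matches it. Criterion 4 is therefore the listed rule that has to carry that statement. As printed, it does not.

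**Step 5: check whether the urine tests themselves are affected.** The visit steps and the flow-chart footnotes depend on *child-bearing potential*, not on the term in footnote a. The phrase occurs eight times: four visit steps, two flow-chart footnotes, and criterion 5 in both the synopsis and Section 5.3.3 (4 + 2 + 2 = 8). It is nowhere defined. Nothing in the protocol says that it is the exact complement of footnote a, so the footnote does not switch the tests off. At V01 the test comes before the criteria check.

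**The case against.** The strongest reply is that this is a one-word slip with its practical risk already contained. The test at V01 precedes the eligibility check, and the flow-charts schedule it again at V03 and the booster visit. A positive result bars later doses, Section 5.3.6.5 states the intent, and the phrase *as applicable* in criterion 4 leaves room for judgement. An investigator would hardly enrol a girl with a positive test by calling her unable to bear a child. All of this stands, and it keeps the point minor. It does not make the printed criterion right: the test produces a result, and criterion 4 is the listed rule meant to act on that result before the first dose.

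A reader might go further and infer that post-menarchal girls would be vaccinated untested, or that the footnote contradicts the testing rules and leaves them applying to almost nobody. The documents do not support either inference. Both need *child-bearing potential* to mean everyone outside footnote a, which the protocol never says. A girl can satisfy criterion 4 by its first limb and still be tested under V01 step 4; the two instructions can both be followed. The conflict is with Section 5.3.6.5 and with the purpose of criterion 4.

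It can also be said that *pre-menarchal* is a guess, since a slip for *post-menopausal* from an adult text is possible. That is fair. The printed word is wrong on either account, and only *pre-menarchal* gives a definition suited to children, but the sponsor should confirm it.

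**Conclusion.** The footnote is wrong as written. Taken literally, it lets practically every girl under 18 meet criterion 4 whatever her urine test shows, and so conflicts with the protocol's own statement that pregnancy excludes. The word is certainly wrong for this population; that *pre-menarchal* was intended is an inference.

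Severity is minor. The error is one word in one footnote. The number of girls concerned cannot be derived from the protocol, and none is claimed. Enrolment of an untested or pregnant girl is not shown. Sample size, endpoints and analyses do not depend on it. It deserves correction because it sits in an eligibility rule that protects minors before an investigational vaccination.

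**What to change.** In footnote a to criterion 4 (Section 5.3.3), replace *pre-menopausal* with *pre-menarchal*, after the sponsor confirms that this was meant. The synopsis has no such footnote and needs no change.

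Optionally, add a sentence to the footnote saying that all other non-sterilized females are of child-bearing potential. That would give the undefined term a meaning for criterion 5 and for the urine tests at V01, V03 and the booster visit. It is a useful tidying step, but the correction does not depend on it.

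The cost is one word, or one word and one sentence, with no effect on design, sample size or analysis.

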### 5.3.4 Exclusion Criteria

***All subjects:***

- 1) Participation in another clinical trial in the 4 weeks preceding the first trial vaccinationa.
- 2) Planned participation in another clinical trial during the present trial period.
- 3) Congenital or acquired immunodeficiency, immunosuppressive therapy such as anti-cancer chemotherapy or radiation therapy within the preceding 6 months, or long-term systemic corticosteroid therapyb.
- 4) Systemic hypersensitivity to any of the vaccine components or history of life-threatening reaction to the trial vaccine or a vaccine containing the same substances (egg proteins, chick proteins, thimerosal, aluminum, neomycin, formaldehyde, and octoxinol 9)c.
- 5) Chronic illness at a stage that could interfere with trial conduct or completiond.
- 6) Blood or blood-derived products received in the past 3 months.
- 7) Any vaccination in the 4 weeks preceding the first trial vaccination.
- 8) Vaccination planned in the 4 weeks following any trial vaccination.
- 9) History of the H5N1 infection (confirmed either clinically, serologically or virologically).
- 10) Known HIV, Hepatitis B (HBsAg) or Hepatitis C seropositivity.
- 11) Previous vaccination with an avian flu vaccine.
- 12) Subject at high riske of the H5N1 infection during the trial.
- 13) Thrombocytopenia or bleeding disorder contraindicating IM vaccination.
- 14) Febrile illness (rectal equivalent temperature  $\geq 38.0^{\circ}\text{C}$ ) on the day of inclusion.

***Children/Adolescents aged  $\geq 2$  years to  $<18$  years:***

- 15) Breast-feeding mothers.
- 16) Current alcohol abuse or drug addiction that may interfere with the subject's ability to comply with trial procedures (if applicable, depending on the subject's age).

***Infants/toddlers aged  $\geq 6$  months to  $<2$  years:***

- 17) History of seizures.

---

a Participation in another clinical trial investigating a vaccine, a drug, a medical device, or a medical procedure.

b Systemic corticosteroid therapy (prednisolone or equivalent) for more than two consecutive weeks within the past 3 months.

c The list of vaccine components is included in the Investigator's Brochure.

d Chronic illness may include, but is not limited to, cardiac, renal or auto-immune disorders or diabetes.

e Subject likely to be in recurrent close contact with poultry (including back-yard chickens and fighting cocks) or wild birds.

### 5.3.5 Temporary Contraindications

Should the following condition occur, the Investigator will postpone the second or booster vaccination until the condition is resolved.

- Acute febrile illness within the 72 hours preceding the vaccination or rectal equivalent temperature  $\geq 38.0^{\circ}\text{C}$  on the day of the vaccination.

Vaccination should be postponed within the timeframe for vaccination indicated in the trial flowchart (see Figure 1 and Figure 2).

For example, in case a subject experiences fever (rectal equivalent temperature  $\geq 38^{\circ}\text{C}$ ) 75 hours before vaccination until 2 hours before vaccination, this subject complies with the temporary contraindication (fever within 72 hours preceding the vaccination). Vaccination will be postponed until there is no fever for  $>72$  hours.

### 5.3.6 Removal of Participants from Treatment or Assessment

Withdrawn subjects will not be replaced.

#### 5.3.6.1 Conditions for Withdrawal

A subject may decide or a subject's parent/legal representative may decide for the subject to stop participating in the trial for any reason and at any time. In this case, the Investigator must determine that the reason for withdrawal is not related to an AE. The reason for a subject withdrawing during the trial will be specified in the source document and in the relevant section of the CRF.

Subjects/parents/legal representatives will be informed that they have the right to withdraw from the trial at any time.

The Investigator will discontinue the second or booster vaccination in the case of an event considered to be a definite contraindication (see following list). The vaccination will be delayed in the event of a temporary contraindication (see Section 5.3.5).

